### Outcome measurement

The primary outcome will be the proportion of utilized hand hygiene opportunities (number of critical times hand hygiene is observed to be done with soap and water or ABHR) out of the total number of observed hand hygiene opportunities. The secondary outcome will be *E. coli* concentration levels in hand rinsates from HCWs, which indicates recent fecal contamination and hand hygiene failure.

We shall determine the two outcome variables using two approaches. Firstly, observations based on the WHO’s 5 moments for hand hygiene which include: before touching a patient; immediately before performing an aseptic procedure; immediately after an exposure risk to body fluids (and after glove removal); after touching a patient and his or her immediate surroundings when leaving as well as after touching any object or furniture in the patient’s immediate surroundings, when leaving - even without touching the patient [37]. Hand hygiene observations will be conducted during the baseline, midline and end-line surveys. The hand hygiene observations will be done in the mornings (8 am – 12 pm) and evenings (4 pm – 8 pm) since these are considered to be peak treatment hours [36]. Within the targeted time, 20 hand hygiene opportunities will be observed for each of the selected HCWs (corresponding to 10 patients each with 2 hand hygiene opportunities, which will include before touching a patient and after touching a patient), and the used and missed opportunities will be recorded. Therefore, a total of 9000 hand hygiene opportunities will be observed by experienced researchers (HCWs or environmental health officers), who will observe from the least obtrusive point within a radius of 5–10 m of the patient wards [38].

Secondly, hand rinsates from HCWs participating in the CRT will be collected immediately after the hand hygiene observations during baseline and end-line. The samples (hand rinsates) will be collected by a team of trained environmental health officers. During sampling of hand rinsates, HCWs will put their hands, one at a time in Whirl-Pak bags containing distilled water. The HCWs will wash their hands by rubbing the inner hands for about 2 min and the enumerator massaging their hands from outside the whirl pak bag to remove any potential pathogens. Aseptic techniques will be used to collect duplicate samples from each of the study participants (HCWs) during baseline, midline and end-line. The samples will be stored in sterile plastic bottles and transported on ice to the laboratory for further analysis within 4 h. The hand rinsates will be analysed for *Escherichia coli (E.coli)*, to establish if there are differences in the levels of contamination on the hands of the HCWs before and after the intervention. During analysis, hand rinsates will be diluted using the ratios of 1:1, 1:10 and 1:100. The membrane filtration method (with Chromocult agar) will be used to concentrate samples, and incubation will be done at 37 °C for 24 h. Colonies of *E.coli* will be identified by their dark blue to violet colour, and they will be counted and recorded per 100 ml of sample.

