A sample size of 30 clusters [HC IIIs and IVs] (15 HCFs under the intervention and 15 HCFs under the control arm) with 15 HCWs per HCF will allow us to detect a 20% increase in the proportion of HCWs that practice hand hygiene (hand washing/hand rub) at the 5 critical moments at 4 months between the control and the intervention groups. The calculation of the sample size is based on the following assumptions: a 25% and 5% increase in hand hygiene in intervention and control group respectively, a standard normal deviate of at 95% confidence level (1.96), a standard normal deviate at 80% power level (0.84), the proportion of HCWs practising hand hygiene in the control group (0.747) from an infection control study in HCFs in Arua district, Northern Uganda [39] and a design effect of 2.0 to account for the fact that there would be clustering of HCWs within HCFs. This gives a sample size of 426, however, in order to achieve a consistent cluster size, the sample size will be rounded off to 450 HCWs participants, with 225 in each of the study arms. The study will recruit 450 HCWs (doctors, clinical officers, nurses and midwives) who work in maternity and children’s wards. In each HCF, the study will target 13 nurses/midwives and 2 Doctors/Clinical Officers.

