Though not widely studied, having simple hand washing facilities such as plastic jerrycans and tippy taps have been shown to increase adherence to hand hygiene at critical times at community level [45, 46]. Therefore, our study will utilise this intervention based on the notion that having simple innovatively designed hand hygiene facilities and the required supplies will increase the level of adherence. In addition to the interventions in the control arm, HCWs in the intervention arm will be exposed to environmental cues and mobile text messages on hand hygiene. Also, evidence from a simulation hospital study in a US medical centre and affiliated medical school indicated that environmental cues subconsciously influenced the hand hygiene practice [47]. Similarly, mobile text messages have also been reported to influence behaviour change in a number of healthcare interventions [48, 49]. However, their impact on promotion of hand hygiene in HCF settings is still understudied [21]. Mobile text messages are anticipated to promote adherence to hand hygiene by reminding HCWs to wash hands or use ABHR during the critical moments of patient care.

The impact of the environmental cues and mhealth intervention will be assessed based on adherence to the WHO’s 5 moments for hand hygiene [50] and *Escherichia coli* (E.coli) concentration levels in hand rinsates from HCWs. The WHO 5 moments of hand hygiene have widely been used in evaluating hand hygiene interventions in healthcare settings [50–52]. Similarly, *E. coli* has also been used as an indicator for measuring the effectiveness of hand hygiene in HCFs [53–55].

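### The endpoint is stated as practice at the WHO 5 moments, but the counting rule fills every planned opportunity with two of them, before and after touching a patient

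*Protocol article*

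**What the plan says.** In the protocol article, Outcome measurement, the primary outcome is the share of observed opportunities that are used, a used opportunity being described as the "number of critical times hand hygiene is observed to be done with soap and water or ABHR". The same section says how this will be measured: "observations based on the WHO’s 5 moments for hand hygiene which include: before touching a patient; immediately before performing an aseptic procedure". It goes on to name the other three moments, among them "immediately after an exposure risk to body fluids (and after glove removal") and "after touching any object or furniture in the patient’s immediate surroundings, when leaving - even without touching the patient".

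Two later sections state the endpoint in five-moment terms. The sample-size text (Data collection methods, respondents and sample size, under the cluster randomized trial) concerns the proportion of workers who "practice hand hygiene (hand washing/hand rub) at the 5 critical moments at 4 months". The Discussion takes the WHO 5 moments as its standard, in a sentence that opens "The impact of the environmental cues and mhealth intervention will be assessed based on adherence to".

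The only rule for what an observer counts is back in Outcome measurement. Each selected worker contributes 20 opportunities, a number that the article explains as "corresponding to 10 patients each with 2 hand hygiene opportunities, which will include before touching a patient and after touching a patient". The article derives its total of 9000 opportunities from that rule.

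**The concern.** The article describes the outcome as covering five moments and then fixes a count made up of two. If observers follow the count, the other three moments have no planned place in the numerator or the denominator of the primary outcome. The trial would then measure something narrower than the endpoint it is powered on and the claim it intends to make.

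There is also a practical risk. Under Masking/blinding, independent teams collect the data in each arm and are trained separately. A rule that can be read in two ways could be settled differently by the two teams, and randomisation gives no protection against that.

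**Working it through.** **Inputs (all from the protocol article)**
- Patients per worker: 10; opportunities per patient: 2, named as before and after touching (Outcome measurement)
- Opportunities per worker: 20; total: 9000 (Outcome measurement)
- Workers: 450, as 30 facilities × 15 (sample-size text)

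**Step 1: reproduce the plan's figures.**
- Per worker: 10 patients × 2 = 20, which matches.
- Total: 450 × 20 = 9000, which matches.

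**Step 2: allocate the quota to the five listed moments.**

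| Moment listed in Outcome measurement | Planned per worker | Planned in the 9000 |
|---|---|---|
| Before touching a patient | 10 | 450 × 10 = 4500 |
| Before an aseptic procedure | 0 | 0 |
| After body-fluid exposure risk or glove removal | 0 | 0 |
| After touching a patient and surroundings, on leaving | 10 | 450 × 10 = 4500 |
| After touching surroundings only | 0 | 0 |
| Total | 20 | 9000 |

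The remainder for the three unnamed moments is 20 − (10 + 10) = 0 per worker. The fourth moment, as the article defines it, already takes in surroundings touched along with the patient, so only contact with surroundings alone is left out.

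**Step 3: does the number of survey rounds change this?** Observations are planned at baseline, midline and end-line. The 9000 equals one round; three rounds at the same quota would be 3 × 9000 = 27,000. The composition is the same in each round, so the point is unaffected.

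**Step 4: what would a five-moment count look like?** Purely as an illustration, if each moment arose once per patient, 10 patients would give 10 × 5 = 50 opportunities per worker, or 450 × 50 = 22,500 per round. Keeping 20 per worker and spreading them evenly would give 20 / 5 = 4 per moment. Neither matches the stated composition. The article does not give the real mix of moments.

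**The case against.** The best defence is that the parenthesis explains how 20 was budgeted and does not restrict what is recorded. Its verb, include, need not be exhaustive. The Evaluation section says the data collection tools follow the 5 moments, and Strengths and limitations says standard WHO observation tools will be used. The evaluation tool (Additional file 5) is not shown and may well have fields for all five. The sentence that formally defines the primary outcome speaks of critical times without saying how many.

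Part of this stands. A reader might infer that the other three moments will certainly go unrecorded; the documents do not establish that. The conflict remains, though. Each patient contributes exactly two opportunities, two are named, and both the 20 and the 9000 are built from that count. If the form does collect other moments, the stated composition is wrong.

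A reader might also infer a bias of several points in the treatment effect. For example, if the omitted moments made up 30–50% of real opportunities and compliance there differed by 20 points, measured compliance would shift by 0.3 × 20 = 6 to 0.5 × 20 = 10 points. The documents support neither assumption. The result would also be a shift in level common to both arms, which cannot be set against the 20% increase the trial is designed to detect between arms. The contrast would change only if the intervention worked differently by moment, or if the two arms' teams counted differently. The documents give no figure for either.

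Nor do they say that compliance differs by moment, that the omitted moments are especially frequent in delivery rooms, or that they are the ones most closely tied to the *E. coli* outcome. The point does not rely on any of these.

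Finally, a fixed before-and-after pair has a real merit: every worker in both arms contributes the same mix of moments.

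**Conclusion.** The inconsistency is real and should be resolved, but it concerns the scope and labelling of the primary outcome. Its size is a count: three of the five listed moments have 0 of the 9000 planned opportunities. This rests on reading the two-per-patient rule as the sampling rule, which is the natural reading because it reproduces both stated totals exactly. Some doubt remains about what the unseen form records.

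A trial run as written supports a conclusion about hand hygiene before and after patient contact. It does not support one about adherence to the 5 moments. For the two moments counted, the comparison between arms is not itself biased, provided both observer teams apply the same rule. No numerical effect on the estimate can be derived from the documents.

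**What to change.** Before baseline, settle one counting rule and train both arms' observer teams on it. There are two ways to do this.

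1. **Keep the two-moment count and restate the outcome.** Describe the primary outcome, the sample-size endpoint and the planned conclusions as hand hygiene before and after patient contact, and drop the five-moment claim. The cost is rewording only, and the uniform mix of moments is kept.
2. **Keep the five-moment outcome and change the count.** Let each worker's 20 opportunities be any of the five moments, record the moment type for each, and report compliance by type. The cost is a revised counting rule and, if the form lacks it, a field for moment type. The small downside is that the mix of moments will then vary between workers, which is why the results by type are needed.

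The choice depends on which claim the sponsor wants to make. Either one removes the contradiction.

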**Methods:**

The study is a cluster-randomized trial, which will be guided by the behaviour centred design model and theory for behaviour change. During the formative phase, we shall conduct 30 key informants’ interviews and 30 semi-structured interviews to explore the barriers and facilitators to HCWs’ HH practice. Besides, observations of HH facilities in 100 HCFs will be conducted. Findings from the formative phase will guide the intervention design during a stakeholders’ insight workshop.

The intervention will be implemented for a period of 4 months in 30 HCFs, with a sample of 450 HCWs who work in maternity and children’s wards. HCFs in the control arm will receive innovatively designed HH facilities and supplies. HCWs in the intervention arm, in addition to the HH facilities and supplies, will receive environmental cues and mhealth messages. The main outcome will be the proportion of utilized HH opportunities out of the 9000 HH opportunities to be observed. The secondary outcome will be *E. coli* concentration levels in 100mls of hand rinsates from HCWs, an indicator of recent fecal contamination and HH failure. We shall run multivariable logistic regression under the generalized estimating equations (GEE) framework to account for the dependence of HH on the intervention.

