### Evaluation

We shall conduct process and outcome evaluations. The process evaluation will be conducted at the midline to understand how the intervention has been implemented. The process evaluation will seek to establish: whether the intervention is being implemented according to plan; whether the intervention is working or not; how many HCWs will be getting exposed to the touch points; how many HCWs will be responding to the mhealth intervention as well as the aspects of the intervention that participants will have liked. The baseline, midline and end-line evaluations will be conducted using a tool provided as Additional file 5.

To assess the outcome of the intervention, a structured questionnaire will be administered at baseline, midline (2 months after starting intervention) and end-line (4 months) as indicated the participants’ timeline in Fig. 2. During surveys, social demographic, knowledge and attitudes questions will be collected from all participating HCWs through an interviewer administered questionnaire. The questionnaires will be administered to the HCWs before the hand hygiene observations. In order to maintain systematic consistency for measurement indicators, the same research tools used at baseline will be used for mid-term, end-line and impact evaluation. In addition, observations of hand hygiene practice among the HCWs will be done at baseline, midline and end-line using an observation tool. Hand rinsates will be collected and analysed, and the results will be entered in a hand rinsates form. All the data collection tools to be employed will be guided by the WHO’s 5 moments for hand hygiene [37].

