#### Data analysis

i.Qualitative analysis (formative stage)

The KIIs will be transcribed verbatim by two experienced transcribers. The typed transcripts will then be read several times by all members of the study team who will then develop codes. Code book definitions will be based on the objectives of the study while integrating in emerging themes from the data. The code book will be discussed and agreed upon by the study team. Then two experienced research assistants (RAs) will code the articles using ALTAS-ti software to ease further analysis. The code reports will then be read and discussed by all the investigators who will agree on both codes and categories. Then, codes will be grouped into categories, themes and subthemes [40].
ii.Quantitative analysis (effect of intervention)

The effect of the intervention will be evaluated at two time-points: midway the intervention, and immediately after the completion of the intervention period to assess the short-term effects on hand hygiene. Data from all surveys will be double entered into Open Data Kit (ODK) collect, and statistical analysis will be carried out using Stata version 14. We will calculate the prevalence of cluster level hand hygiene at baseline and follow-up for each HCF. Mixed sub-group analysis will be stratified by sex, cadre, experience, and level of training. We shall run multivariable logistic regression under the generalised estimating equations (GEE) framework to account for the dependence of hand hygiene on the intervention in a marginal way. This approach will give population average estimates for effect of intervention while accounting for other covariates in the model. An exchangeable correlation structure will be considered. Table 3 provides a summary of the study objectives, methods and data analysis procedures.

**Table 3 Tab3:** Summary of study objectives, methods and data analysis procedures

Objectives	Study population	Data collection methods	Indicators	Data analysis
Explore the facilitators for enhancing healthcare workers’ hand hygiene practices in HCFs in the GKMA.	Healthcare workers in selected HCFs and district leaders.	Key informant interviews	Facilitators of Hand hygiene among HCWs	i. Thematic content analysis
		Semi-structured interviews	Facilitators of Hand hygiene among HCWs	i. Thematic content analysis ii. Descriptive statistics
	Healthcare facilities	Observations	Facilitators of Hand hygiene among HCWs	i. Descriptive statistics

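### The 9000 opportunities given as the overall total and the primary-outcome denominator are one survey's worth out of three, and the primary outcome names no time point

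*Protocol article*

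**What the plan says.** The abstract (Methods) states: "The main outcome will be the proportion of utilized HH opportunities out of the 9000 HH opportunities to be observed". Outcome measurement defines the primary outcome as opportunities used "out of the total number of observed hand hygiene opportunities". Neither definition names a survey or a time point.

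On the amount of observation, Outcome measurement says that "20 hand hygiene opportunities will be observed for each of the selected HCWs", made up of 10 patients with 2 opportunities each, and then draws the total: "Therefore, a total of 9000 hand hygiene opportunities will be observed by experienced researchers". The sample-size section says "The study will recruit 450 HCWs".

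On the schedule, Outcome measurement says: "Hand hygiene observations will be conducted during the baseline, midline and end-line surveys". The Evaluation section repeats that "observations of hand hygiene practice among the HCWs will be done at baseline, midline and end-line using an observation tool", and places midline at 2 months and end-line at 4 months.

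On timing of the comparison, Data analysis (item ii) says: "The effect of the intervention will be evaluated at two time-points: midway the intervention, and immediately after the completion of the intervention period". It does not call either one primary. The sample-size section bases the calculation on the difference between arms at 4 months.

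**The concern.** A count that fits a single survey is presented as the total for a trial with three surveys, and the abstract builds that count into the primary outcome. A reader cannot tell whether the 9000 means all observations, those of one survey, or a thinner sample spread over three.

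The missing time point adds to this. Taken literally, a proportion of all observed opportunities includes baseline, when no facility has yet received the intervention. Leaving baseline out, there are still two follow-up surveys at which the effect is to be evaluated, and the outcome definition does not say which one gives the primary result. That should be fixed in the outcome definition itself, not left for the reader to infer from the sample-size paragraph.

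**Working it through.** **Inputs**
- Facilities: 30, with 15 workers each (sample-size section, item iv).
- Opportunities per worker: 20, from 10 patients × 2 (Outcome measurement).
- Observation surveys: 3 (Outcome measurement and Evaluation).
- Stated total: 9000 (abstract and Outcome measurement).

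**Step 1. Reproduce the stated figure.**
Workers: 30 × 15 = 450.
Opportunities: 450 × 20 = 9000.
The figure reproduces exactly, with each worker counted once at 20 opportunities. The number of surveys does not enter.

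**Step 2. Apply the schedule.**
Three surveys: 9000 × 3 = 27,000.
Two follow-up surveys only: 9000 × 2 = 18,000.
The stated total is 9000 / 27,000 = one third of what the schedule implies.

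**Step 3. Try the other readings.**
- *9000 is the whole-trial total, spread equally over surveys.* Then 9000 / 450 / 3 = 6.67 opportunities per worker per survey. This is not a whole number and does not fit 10 patients × 2.
- *9000 refers to one unnamed survey.* Then it is not the total, and the outcome definition still has to say which survey is meant.

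So three equal surveys, 20 opportunities per worker at each, and a total of 9000 cannot all hold.

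**Step 4. Compare the statements on timing.**

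| Place | Time point |
|---|---|
| Abstract, main outcome | none named |
| Outcome measurement, primary outcome | none named |
| Sample-size section | 4 months |
| Data analysis, item ii | midway and end of intervention, unranked |
| Table 3 | change in opportunities used; no time point named |

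Only the sample-size section singles out one time point, and it does so as the basis of a calculation, not as part of the outcome definition.

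**Step 5. Check for knock-on effects.**
The sample size is counted in workers (426, rounded to 450). The 9000 is derived from the 450 and is not an input to it, so neither sample-size figure changes.

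**The case against.** The product 450 × 20 is correct, and since the 20 opportunities are tied to the morning and evening observation windows, the natural reading is 9000 per survey. On that view only the words *per survey* are missing. This largely stands: the 27,000 is an inference, and the defect is in how the outcome is described, not in the multiplication. But the article gives 9000 in two places, once as a total and once as the outcome denominator, and neither fits its own schedule. A fuller protocol or analysis plan would not make these published statements consistent.

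On timing, end-line can be inferred as the deciding time point because the sample size targets 4 months, and the Evaluation section places the process evaluation at midline. This also stands: the statements do not contradict each other outright. What remains is that the outcome definition leaves the time point open.

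Two stronger readings are tempting, and the document supports neither.

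- *Pooling baseline with follow-up would dilute the effect.* With three equal surveys, full effect from midline and the 20% increase read as percentage points, the pooled difference would be 20 × 2/3 = 13.3 points. But no such pooling is planned. Data analysis computes facility-level prevalence separately at baseline and follow-up, and Table 3 uses change as its indicator.
- *Two evaluations inflate the false-positive rate.* If success at either time point sufficed, each tested at 5%, the rate would be 1 − 0.95² = 9.75% under independence, or 7.8% to 9.5% for assumed correlations from 0.8 down to 0.3. The article says the effect is evaluated at two points, states no either-one-suffices rule and gives no correlation. Handling of multiplicity may also sit in an analysis plan that is not shown.

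**Conclusion.** The point holds as an ambiguity in the definition of the primary outcome. The stated total of 9000 is one third of the 27,000 implied by the schedule, assuming that the 20 opportunities per worker apply at each of the three surveys. The article does not state that assumption, but the equal-split alternative of 6.67 per worker per survey is incompatible with 10 patients × 2. Separately, the primary outcome has no time point, and midline and end-line are listed without rank although the trial is sized for 4 months.

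The documents do not show a biased planned analysis, an inflated error rate or a wrong sample size. The correction is still worth making, because it settles at little cost which proportion is the primary result.

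**What to change.** 1. In Outcome measurement, state 9000 planned opportunities per survey (27,000 in total), or give the intended split if it differs.
2. Define the primary outcome as the proportion of opportunities used among those actually observed at end-line (4 months). Keep 9000 as a planned count and not as a fixed denominator, since workers may be lost or fewer opportunities may occur.
3. Name the midline comparison as secondary.
4. Adjust the GEE model for baseline compliance, entered as the worker-level or facility-level baseline proportion.
5. Bring the abstract, Outcome measurement, Data analysis (item ii) and Table 3 into line.

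Items 1 and 5 are wording. Items 2 to 4 are analysis decisions, but they need no new data: baseline observations are already scheduled and the sample size already targets 4 months. By the Trial status section, the study was still in its formative phase and the intervention had not begun, so at that stage the change could have been made before any follow-up data existed.
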